## What is the intervention and proposed duration of treatment?

### a. Co-bedding care

Following randomization to the co-bedding group, twin infants will be placed together in a Giraffe Incubator or crib lying side-by-side. Twins will be diaper clad and nested together in boundaries consistent with neonatal care practices. Larger infants may be partially clothed if in an open crib but still able to freely touch one another and remain nested together. Twins will be positioned close to each other (lying face-to-face, back-to-back, or in spooning positions), permitting contact between them. All infants will have cardio-respiratory monitoring while co-bedding. One side of the incubator/crib will be for twin 'a' and one side will be for twin 'b' and infants and their equipment will be colour coded. Incubator temperatures will be determined using clinical reasoning, anticipated neutral thermal environmental needs (based on infant weight, gestational and post natal age) and incubator settings prior to initiation of co-bedding. If servo temperature regulation is required, most likely in the case of younger twin pairs or discordance in infant weights, the servo probe will be placed on the larger infant. Infant temperatures will be closely monitored and recorded throughout the co-bedding condition to maintain normal axilla readings between 36.8 and 37.2 degrees Centigrade.

All infants will be co-bedded for no less than 24 hours prior to heelstick to allow for stabilization following transfer. The heelstick being studied will occur no greater than 10 days following initiation of co-bedding. Duration of co-bedding will be recorded and controlled for in the analysis if necessary. Limiting the length of co-bedding duration decreases the degree of variance possible for this variable yet still allows adequate time for a heelstick to be ordered as part of usual care.

The medically indicated heelstick will be performed by a designated group of experienced nurses and lab technicians who have performed heelstick procedures in previous studies in the NICU in a standardized manner according to the institutional and unit policy. The nurse assigned to care for the twin will assist with the heelstick procedure. Their role will be to provide non-pharmacologic measures as per the NICU pain guidelines as they would do normally. None of the members of the research team or nurses conducting heelstick will prompt the bedside nurse to alter their care in any way. All non-pharmacologic strategies for pain relief implemented by the nurse including number of 24% sucrose doses given will be recorded and confirmed with video recorded data.

Infants assigned to the co-bedding group, may continue co-bedding, should their parents choose, up to 48 hours prior to discharge at which time monitors will be disconnected and the infants separated.

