## What is the proposed frequency and duration of follow-up?

Data will be collected simultaneously on both the infant undergoing the heelstick and his/her twin. Data collection using monitoring (Somté and Massimo oxygen saturation systems) and video-tape recording will take approximately 20 minutes per participant - a baseline period (1-2 minutes prior to heelstick), warming (2-3 minutes), heelstick (2-5 minutes), and recovery phase (approximately 1-10 minutes).

If both infants require a medically indicated heelstick on the same day, they will occur no less than 30 minutes apart.

All chart data will be collected following randomization and data collection will continue until completion of the heelstick. Prior painful procedures will include all procedures from birth until completion of heelstick.

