We based our PIPP score assumptions on previous studies which reported PIPP scores of 10.7 (2.3) vs. 12.9 (2.5) from a study on kangaroo skin-to skin care versus incubator care in preterm infants 32-36 weeks of gestational age [61] and PIPP scores 8.9 (*CI *7.9-9.9) versus 10.7 (*CI *9.6-11.8) in preterm infant 28-31 6/7 weeks of gestational age. Based on these reported 0.5 and 0.6 standard deviation pain scores [66] and the reported values in the above studies, we used a conservative standard deviation estimate of 2.0 as our proposed study population will encompass both groups of infants. Sample size was calculated using a 2-sided alpha error of 0.05 and a power of 80 percent. We designed the study to detect a difference of 1 point or greater change (SD 2.0) in the PIPP scores. One hundred and twenty-eight infants would be required to identify this variation in the PIPP scores if such a difference is in fact caused by co-bedding. With this sample size, we will also have over 95% power to detect a greater than 15 second mean difference in physiological recovery (heart rate and oxygen saturation) between groups. In a recent study of skin-to-skin care [66], the time to return to baseline heart rate following the application of the plaster signifying the end of the procedure was significantly different, 123 seconds (*CI *103-142) for the Kangaroo Mother Care condition and 193 seconds for Incubator condition (*CI *158-227, *p *< .00001). Since all infants will receive 24% sucrose, we do not expect that the differences seen in time to recovery will be this large. Therefore, by using the larger sample, and conservatively accounting for the use of regression techniques, our study will recruit 128 participants (64 sets of twins, 32 assigned to the co-bedding group and 32 to the standard group).

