## What is the proposed type and frequency of analysis?

Analysis and inference will be based on the intention-to-treat principle. Efforts will be made to ensure that follow up is complete for all subjects and that there are no missing values for any of the subjects for any variable. Blinding of independent coders will be retained until after the analysis is completed. Baseline characteristics of study subjects will be contrasted to ascertain that randomization has in fact produced comparable groups with respect to all variables that effect pain response and physiologic stability. The primary outcome of interest will be the pain response of the infant experiencing a tissue breaking procedure while co-bedding with his/her twin when compared to a twin infant experiencing a tissue breaking procedure receiving standard care (alone in incubator or crib). This analysis will compare the means in the two groups before and after treatment and contrast the mean difference between groups using 95 percent confidence intervals and a p value. The stratified nature of the randomization will be accounted for in the analysis. Also, since twin pairs will be randomized together (i.e. to co-bedding or standard care), the analysis will be corrected for potential non independence of outcomes between twin pairs This will involve appropriate variance adjustment which will be carried out using Generalized Estimating Equations (GEE) procedures using SAS software (Proc Genmod, SAS 8.2, SAS Institute Inc. Cary, NC) [77]. If differences are noted in baseline characteristics, inferences will be made based on observed and (linear regression) adjusted differences between groups. Analysis for secondary outcomes will be done in an identical fashion as pain response and recovery by comparing the mean changes in the two groups before and after treatment and contrasting the mean differences between groups using 95 percent confidence intervals and a p value.

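### Co-bedding duration arises after randomisation and in one arm only, so it does not belong in the between-arm model; one fixed model should govern the primary result

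*Protocol article*

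**What the plan says.** Under Co-bedding care, the protocol article sets a lower bound on exposure: "All infants will be co-bedded for no less than 24 hours prior to heelstick to allow for stabilization following transfer". The upper bound is stated separately: "The heelstick being studied will occur no greater than 10 days following initiation of co-bedding". It then adds: "Duration of co-bedding will be recorded and controlled for in the analysis if necessary". It gives no criterion for necessity, no model form and no value for controls. Under Standard care, control pairs stay in separate incubators and may have the study heelstick at any point after randomisation, up to 10 days.

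The section on type and frequency of analysis defines a comparison of means, corrected for twin pairs by GEE and taking account of the stratified randomisation. It then says: "If differences are noted in baseline characteristics, inferences will be made based on observed and (linear regression) adjusted differences between groups". It does not mention co-bedding duration.

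The Sample Size section takes a two-sided alpha of 0.05 and 80% power. Its target is given as: "We designed the study to detect a difference of 1 point or greater change (SD 2.0) in the PIPP scores". The resulting recruitment figure is 128 infants, that is 64 pairs with 32 pairs in each arm.

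**The concern.** A covariate in a randomised comparison should be fixed before treatment starts and defined in the same way in both arms. Co-bedding duration is neither. It is a dose of the intervention, and its length depends on when a medically indicated heelstick happens to be ordered. Once it stands beside the arm indicator, the two variables share much of the same information. The arm coefficient then no longer estimates the average effect of being assigned to co-bedding, and its standard error rises.

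The imbalance rule raises a separate and milder question. Covariates chosen because they happen to differ between arms are not chosen for prognostic strength. Basing inference on both an observed and an adjusted difference, with neither named as primary, leaves the choice until after the data are seen.

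**Working it through.** **1. The plan's own figure.** Inputs from the Sample Size section: difference 1, SD 2.0, two-sided alpha 0.05, power 80%. The normal approximation gives 63 per arm (126 in total). The exact t calculation gives 64 per arm (128 in total, power 80.1%), so the stated 128 is reproduced. The section says the number allows for regression methods, but 128 is the plain two-sample t-test figure and holds no reserve. Like the plan's calculation, what follows treats infants as independent.

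**2. Precision with duration in the model.** Let T be arm (1:1) and D duration, with D = 0 in controls and mean m and variance v in the co-bedding arm. Over all infants, Var(D) = v/2 + m²/4, Cov(T, D) = m/4 and Var(T) = 1/4. Then R² = (m/4)² / [Var(T) × Var(D)], and the variance inflation factor is VIF = 1/(1 − R²) = 1 + m²/(2v).

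For D uniform on 1 to 10 days (assumed), m = 5.5 and v = 81/12 = 6.75:
- Var(D) = 3.375 + 7.5625 = 10.94 and Cov = 1.375
- R² = 1.375² / (0.25 × 10.94) = 0.69, so VIF = 3.24
- SE without duration: 2 × √(2/64) = 0.354. With duration: 0.354 × √3.24 = 0.636
- Power = Φ(1/SE − 1.96): 81% without duration, 35% with it
- Detectable difference at 80% power: (1.96 + 0.84) × 0.636 = 1.78 points, against about 1.0
- Infants needed for 80% power: 126 × 3.24, about 409

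The protocol gives no distribution of duration, so a range was tried:

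| Assumed duration (days) | VIF | SE | Power |
|---|---|---|---|
| 1 + exponential, mean 2 (not cut at day 10) | 2.1 | 0.515 | 49% |
| Uniform 1–10 | 3.24 | 0.636 | 35% |
| Uniform 1–5 | 4.4 | 0.740 | 27% |
| Uniform 1–3 | 7.0 | 0.935 | 19% |

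A simulation of 4,000 trials under uniform 1–10 agreed: power 79% without duration and 34% with it.

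**3. Meaning of the coefficient.** Suppose the benefit at duration D is a + bD and the average benefit is 1 point at m = 5.5 days. The raw-coded arm coefficient is a:
- benefit growing linearly from zero (b = 1/5.5): a = 0
- constant benefit (b = 0): a = 1
- waning benefit (b = −1/5.5): a = 2

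The same average effect can therefore appear as 0, 1 or 2.

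**4. Dependence on coding.** If D is centred on its mean within the co-bedding arm and set to 0 in controls, it is uncorrelated with T. In the simulation the SE stayed at 0.353 and power at 79%.

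**5. The imbalance rule.** The simulation had ten baseline covariates jointly explaining 30% of variance (assumed), with adjustment only for those differing at p < 0.05.

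| Analysis | Mean estimate (true 1) | SE | Power |
|---|---|---|---|
| Unadjusted | 0.992 | 0.353 | 79.2% |
| Imbalance-selected | 0.995 | 0.355 | 79.8% |
| All covariates pre-specified | not recorded | 0.308 | 90% |

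Type I error was 4.0% for the imbalance-adjusted result alone and 5.4% when the better of observed and adjusted was taken. With smaller explained variance, SE = 0.354 × √(1 − R²): 10% gives 0.335 and power 85%; 20% gives 0.316 and power 89%.

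**The case against.** The strongest reply is that the duration sentence is conditional, that duration is absent from the section defining the primary analysis, and that coding is a detail a statistical analysis plan would settle. This stands in part. A reader might infer that the trial will be analysed at 35% power, or that a real effect will vanish. The documents do not support either. The loss needs raw coding and an assumed distribution, and a null coefficient needs a benefit that grows linearly from zero. The reply does not rescue the sentence itself, however. It is a stated rule, not an omission. Its plain reading is ordinary covariate entry, and an undefined trigger lets the decision follow the data. Centring restores precision, but the variable is still measured after randomisation and in one arm only.

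Three further inferences should be resisted.
- That imbalance-triggered adjustment distorts the treatment coefficient or loses precision. Step 5 shows it does neither relative to the unadjusted analysis.
- That the mention of linear regression abandons the twin correction. GEE with an identity link fits a linear regression mean model, and GEE is specified just before.
- That the plan uses a contaminated baseline covariate because "Prior painful procedures will include all procedures from birth until completion of heelstick". The article lists that count under Other outcomes and never names it for adjustment. Its window matters only if it is used that way.

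It is also fair that the analysis section already takes account of the stratification, which covers gestational age and site.

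**Conclusion.** The point holds in two parts of unequal weight. The first is that the protocol permits control for a component of treatment that arises after randomisation and in one arm only. Entered raw, it turns the arm effect into an extrapolation to zero days and cuts power from about 80% to about 35% (19% to 49% over the distributions tried). Those figures rest on raw coding, an assumed duration distribution and independent infants. They describe what the rule would do if exercised, not the trial's expected power.

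The second, lesser part is that imbalance-triggered adjustment with two unranked results leaves a choice open after the data are seen. Its measured cost is small: type I error of at most 5.4%, plus a forgone gain to roughly 85–90% power if pre-specified covariates explain 10–30% of variance, a share the documents do not give. The change should be made before the data are analysed.

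**What to change.** - Remove co-bedding duration from the between-arm model. Examine it only within the co-bedding arm, as an exploratory dose-response, noting that duration there is not randomised.
- Name one GEE model as primary, fitted whatever the observed balance: arm, gestational-age stratum, site, and any prognostic baseline covariates listed in advance and measured by randomisation. Report the unadjusted difference as supportive.
- If prior painful procedures are used as a covariate, count them only up to randomisation. The count to completion of the heelstick can stay as the outcome already listed.

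The cost is analysis wording; no extra infants or visits are needed. The one practical check is whether the chart abstraction dates each procedure, since the article does not say so and a count cut at randomisation depends on it.

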### d. Inclusion criteria

All medically stable twin infants admitted to the NICU of the IWK Health Centre and St. Justine Hospital will be eligible for the study. Twins will be deemed to be medically stable if they are:

a. Free from infection, and

b. Breathing room air or receiving oxygen via nasal prongs.

Twins may be receiving feeds via gavage tubes, IV therapy via peripheral or central line, and may be experiencing periods of apnea.

Additionally, parents of the twins must understand written and spoken English or French.

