### b. Standard care

For infants who are randomized to receive standard care, the twin pair will remain in separate incubators as per current NICU policy. The twins will be nested in boundaries consistent with neonatal care practices. The heelstick may occur at any time following randomization but within 10 days to maintain consistency between groups. Twins will undergo a medically indicated heelstick in the incubator or crib in an identical fashion as outlined above.

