## Ethics

Authorization and informed consent will be obtained from a parent(s) of eligible twins prior to study entry. The IWK Health Centre, Ste. Justine Hospital and McGill University Research Ethics Board have approved this study. The principal investigator or site research nurse will explain the research study to the parents if twins meet the study criteria. Parents will read the Consent/Authorization Form and any questions they may have concerning the research study will be answered. The Consent/Authorization form will contain information on potential risks and benefits to the participants, research rights of the participant, and information on how to contact the invetigator or study nurse. Participation in the study will be voluntary. Parents will be made aware of their right to withdraw their children at any point in the course of the study. Consent forms will be provided in English or French and a copy will be provided to participants once signed.

Co-bedding is considered to be a safe practice for twins. Nevertheless, a careful watch will be kept on all study participates with regard to any possible adverse effects of co-bedding. Infants will be monitored as per the NICU Care Unit standard of care and their clinical condition will be evaluated daily as part of medical rounds and by the study team. Heelstick procedures are an aspect of usual care for infants in the NICU and will not be conducted solely for the purpose of this study. Study participation will not interfere with routine care practices. Routine strategies for pain relief including sucrose administration and non-pharmacologic measures will be provided as per standard IWK Health Centre NICU care.

Co-bedding twins is not considered to be a standard of care in the NICU. This study provides no direct benefit for the parents or infants enrolled. Compensation will not be offered. There will be no study restrictions regarding the continued practice of co-bedding until 48 hours prior discharge for those infants allocated to the co-bedding group

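### The study-heelstick window opens later and closes earlier under co-bedding than under standard care, with no minimum expected stay, so near-discharge pairs can give a conforming primary outcome only in standard care

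*Protocol article*

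**What the plan says.** All references are to the Protocol article.

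- **Start of the window, co-bedding** (a. Co-bedding care): "All infants will be co-bedded for no less than 24 hours prior to heelstick to allow for stabilization following transfer".
- **End of the window, co-bedding** (same section): "The heelstick being studied will occur no greater than 10 days following initiation of co-bedding". The section also lets parents continue co-bedding "up to 48 hours prior to discharge at which time monitors will be disconnected and the infants separated". The Ethics section repeats the limit: there are "no study restrictions regarding the continued practice of co-bedding until 48 hours prior discharge" for that arm.
- **Window, standard care** (b. Standard care): "The heelstick may occur at any time following randomization but within 10 days to maintain consistency between groups". No pre-discharge limit is given.
- **Eligibility** (d. Inclusion criteria) is set broadly: "All medically stable twin infants admitted to the NICU of the IWK Health Centre and St. Justine Hospital will be eligible for the study". Neither the inclusion nor the exclusion criteria mention expected discharge. The Study population section requires at least one medically indicated heelstick but does not say when it must fall.
- **Analysis** (What is the proposed type and frequency of analysis?): the primary comparison sets a heelstick performed during co-bedding against one performed in standard care. It is by intention to treat, with the aim of having no missing values. No rule covers a co-bedded pair that reaches separation before its study heelstick.

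**The concern.** The heelstick is ordered for clinical reasons, so whether a randomised infant yields a primary outcome depends on how long its window stays open. By the stated rules that length depends on the arm, and the difference matters most for pairs close to going home. Such pairs may well be eligible: all medically stable twins qualify, and the co-bedding section expects some larger infants in open cribs.

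If a near-discharge pair in the co-bedding arm has no qualifying heelstick, there are two possibilities. Its outcome may be missing, while the matching pair in standard care is measured; the groups actually compared can then differ in maturity and health. Or it may be measured after separation, and then it carries little or none of the intervention into the intention-to-treat contrast. Stratifying at 32 weeks does not prevent either, because the problem arises after randomisation. The standard-care section gives consistency between groups as the reason for its 10-day limit, so the unequal windows also miss the protocol's own aim.

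**Working it through.** **The plan's own figure.** Inputs from Sample Size: difference 1 PIPP point, SD 2.0, two-sided alpha 0.05, power 80%. The two-sample t-test gives 63.8, so 64 infants per arm and 128 in total, as stated. Power at 64 per arm is 0.801 (t) or 0.807 (normal approximation). This treats infants as independent, as the stated figure does. The requirement and the recruitment target are both 128, so there is no margin for loss.

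**Window lengths.** Let L be the hours of stay left at randomisation, with co-bedding starting at once. Any delay in starting shortens the co-bedding window further.

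- Co-bedding: max(0, min(240, L − 48) − 24)
- Standard care: min(240, L)

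The co-bedding window is empty when L ≤ 24 + 48 = 72 h. The standard-care window is open from hour 0.

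The documents give no heelstick frequency. For scale, assume a constant rate of one per 72 h, so that P(at least one) = 1 − exp(−window/72).

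| L (h) | Co-bedding window (h) | Standard-care window (h) | Chance of an outcome, co-bedding | Chance of an outcome, standard care |
|---|---|---|---|---|
| 72 | 0 | 72 | 0% | 63% |
| 96 | 24 | 96 | 28% | 74% |
| 120 | 48 | 120 | 49% | 81% |
| 168 | 96 | 168 | 74% | 90% |
| 288 | 216 | 240 | 95% | 96% |

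The gap depends on the assumed rate. At L = 96 h, one heelstick per 36 h gives 1 − exp(−24/36) = 49% against 1 − exp(−96/36) = 93%. One per 144 h gives 1 − exp(−24/144) = 15% against 1 − exp(−96/144) = 49%.

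**Both ends matter** (again at one heelstick per 72 h).

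- Adding only a 24-hour wait to standard care leaves 0 against 48 h at L = 72 h (0% against 49%) and 24 against 72 h at L = 96 h (28% against 63%). The gap closes only at L = 288 h (12 days).
- Adding only the pre-discharge cut-off to standard care leaves 24 against 48 h at L = 96 h (28% against 49%).

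**Effect on the trial.** The share f of co-bedding pairs affected is not in the documents, so a range is assumed. Power uses the normal approximation with 64 controls and 64(1 − f) co-bedded infants. If the lost pairs differ from the rest by d points, the retained mean shifts by f × d.

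| f | Co-bedding pairs left (of 32) | Power if missing | Shift for d = 1 to 2 points | Pairs to randomise to keep 32 |
|---|---|---|---|---|
| 2% | 31.4 | 0.803 | 0.02 to 0.04 | 33 |
| 5% | 30.4 | 0.797 | 0.05 to 0.10 | 34 |
| 10% | 28.8 | 0.786 | 0.10 to 0.20 | 36 |
| 20% | 25.6 | 0.760 | 0.20 to 0.40 | 40 |

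If the affected pairs are instead measured apart, and co-bedding has no effect once they are apart (assumed), a true 1-point difference becomes (1 − f) × 1. That is 0.98, 0.95, 0.90 or 0.80 points.

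**The case against.** The strongest reply is that the 48-hour sentence does not define the study window. It comes after the description of the heelstick, is permissive in tone and speaks of optional continuation. The Ethics section frames it the same way, and data collection ends when the heelstick is complete. On that reading only the 24-hour start differs between arms. The reading is possible, but it does not dispose of the point. Neither section limits the rule to pairs already measured, and the co-bedding section has the infants separated at that moment. A pair not yet measured is apart from then on.

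The second reply is that few pairs are likely to be affected. Eligible pairs need a medically indicated heelstick, and the protocol regards its window as allowing adequate time for one to be ordered. This stands in part: at 2% to 5% lost, power hardly moves.

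Third, the protocol has safeguards: co-bedding duration is recorded and controlled for if necessary, compliance with allocation is monitored daily, and baseline differences lead to adjusted estimates. These help with imbalance among measured infants but cannot recover an outcome that was never obtained.

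A reader might infer that near-discharge co-bedding pairs must drop out of the analysis, or that intention to treat fails. The documents do not support that. A heelstick after separation can still be analysed as randomised; the cost is then dilution, not missingness.

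**Conclusion.** The point holds as a difference between arms in the opportunity to be measured. Under the stated rules a conforming co-bedded heelstick needs more than 72 hours of remaining stay, and a standard-care heelstick needs none. For stays from 72 to 240 hours the co-bedding window is 72 hours shorter. This rests on reading the 48-hour separation as applying to every co-bedded pair; if it applied only after the study heelstick, the 24-hour difference at the start would remain.

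Its consequence cannot be sized from the documents, because neither the heelstick frequency nor the distribution of remaining stay is given. Over the assumed 2% to 20% range the harm runs from trivial to moderate: nominal power about 0.80 to 0.76, and a possible shift of 0.02 to 0.4 points against a 1-point target. Arm-dependent loss matters more than lost power.

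It would go too far to infer that the sample size is wrong, since 128 reproduces, or that many pairs are affected, since nothing in the protocol shows this. The point is worth correcting before recruitment because the correction is cheap.

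**What to change.** 1. In the co-bedding and standard-care sections, define one study-heelstick window for both arms. It opens 24 hours after allocation is implemented and closes at the earlier of day 10 and 48 hours before planned discharge. At L = 96 h this gives 24 hours in each arm.
2. Add to the inclusion criteria that both twins are expected to stay in the study NICU for more than 72 hours after randomisation. This line alone is not enough, because unequal windows would still leave unequal opportunity for pairs just above the threshold.
3. In the analysis section, state that a pair measured outside the window stays in the intention-to-treat analysis as randomised.

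These changes concern which heelstick is used as the study measurement. The clinical rule on separating twins before discharge is not altered.

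**Cost.** A few near-discharge pairs are not recruited, and some early or late control heelsticks are no longer used as the study heelstick. Expected discharge is only an estimate at randomisation, so some pairs will still leave early and some with short stays will give no outcome in the window. Under a common window, however, the opportunity for an outcome is the same in both arms.
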